### Study aims for the intervention development study and the trial protocol

The aim of this article is twofold: First, we report the participatory development of a school-based prevention program addressing vaping and smoking, tailored to the context of schools serving students from lower socioeconomic backgrounds. Second, we present the protocol for a longitudinal cluster-randomized controlled trial designed to evaluate the program’s effectiveness in strengthening students’ intention to remain nicotine-free and in reducing nicotine initiation and consumption. In addition, the study will examine the mediating mechanisms of program effects to identify which intervention components are critical to the success of vaping and smoking prevention. We will also explore heterogeneity in risk and protective factors, intervention effects, and mechanisms of action according to students’ social determinants of health. The results may therefore provide insights into group-specific needs and inform differentially effective prevention strategies.

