### Cluster-randomized controlled trial protocol

The primary objective of the trial is to assess the effects of a school-based prevention program with three training sessions on motivation, smoking, and vaping (primary outcome: intention to be vape- and smoke-free across all modes of use) in children in Grade 5 (Age: 10–11 years) at 3, 6, and 12 months after baseline, compared to an active control group receiving the standard curriculum. Smoking and vaping measures include the use of cigarettes, disposable e-cigarettes, reusable e-cigarettes, hookah, tobacco heater, cigars/cigarillos, and pipe.

We will report intervention content based on the well-established Behavior Change Technique Taxonomy^49^ and examine underlying mediators of the program effects. We will recruit students from schools with elevated sociostructural burden and examine risk and protective factors, intervention effects and mechanisms of action in relation to students’ SDOH. The assessment and analysis of both mediating mechanisms and SDOH as moderators are expected to advance a “precision approach” to prevention – bringing us closer to providing the right preventive intervention to the right person at the right time and in the right place^31,57^.

We hypothesize that children in the intervention group, compared with children in the control group, will exhibit

Increased intentions to be vape- and smoke-free (primary endpoint measured at the 12-month follow-up) andDecreased susceptibility to vaping/smoking; vaping/smoking prevalence (lifetime prevalence, 12-month and 30-day prevalence, as well as 30-day-frequency), regular vaping/smoking (≥ once a week), and current vaping/smoking (≥ once a week during the last month).The intervention effects are mediated via 
increased action planning for vaping/smoking refusal; increased vaping/smoking refusal skills (i.e., refusal self-concept and refusal self-efficacy as proxies for actual capabilities); increased self-efficacy to be vape- and smoke-free; increased positive attitudes towards being vape- and smoke-free,increased stress and problem coping (i.e., self-efficacy and planning for coping); and heightened intentions to be vape- and smoke-free (for the outcomes of susceptibility and vaping/smoking behavior only); decreased perceived vaping/smoking norms; decreased negative attitudes towards being vape- and smoke-free.

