We will further test hypotheses about differences in risk and protective factors, as well as in vaping/smoking outcomes, by SDOH subgroups (gender, SES, religion/world view, migration history, spoken language, and health status). A detailed description of this examination can be found in our pre-registration file^37^. Additionally, we will explore differential intervention effectiveness as well as underlying mechanisms of change by subgroup.

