### Analysis

The analyses on intervention effects will be conducted on an intention-to-treat basis, including data from all students based on the groups they were randomly assigned to. The main confirmatory analysis pertains to the group difference between intervention and control group in intention to be vape- and smokefree at the 12-month follow-up (T4), adjusted for baseline (T0). All other analyses, including analyses of secondary behavioral outcomes and additional time points, will be considered secondary or exploratory, and no formal multiplicity adjustment will be applied.

Group differences in secondary behavioral endpoints (i.e., prevalence and frequency measures) will be analyzed across all product categories (e.g., prevalence defined by the use of at least one of the products presented in the questionnaire) as well as individually for each product reported by at least 1% of the sample.

For continuous and dichotomous outcomes, we will use generalized mixed effect regression analyses (i.e., linear regression for the outcome of intention to be vape- and smoke-free; logistic regression for [binary] susceptibility, prevalence measures, current vaping/smoking and regular vaping/smoking). The primary analyses will use a two-level structure, with students at Level 1 nested within schools at Level 2, reflecting the school-level randomization and the role of the school as the primary clustering unit. In regard to count data, we will use Generalized Estimating Equations to conduct zero-inflated negative binomial regressions for count outcomes with many zeros, i.e., the 30-day frequency. We will investigate intervention effects using the criterion of statistical significance (*p* < 0.05) of the regression coefficients for the treatment condition variable (adjusting for prespecified baseline covariates; all measured at T0: intention, age, gender, parental vaping/smoking, best friend’s vaping/smoking, objective socioeconomic status, school attachment, self-esteem and distress). All models will be specified with a maximal random effects structure and progressively simplified as needed to reach convergence.

To handle missing data appropriately, we will conduct a comprehensive analysis of attrition patterns, multiple imputation and sensitivity analyses to check the robustness of our inferences to departures from the underlying assumption of missingness at random.

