We will initially test the hypothesized mediators of intervention effects in simple mediator models before proceeding with a multiple mediation analysis. All mediation analyses will account for the nesting of students within schools using mixed-effects modelling approaches.

*Program evaluation by social determinants of health.* We will investigate SDOH subgroup differences in absolute levels of risk factors and outcome variables, as well as differential predictive power of those risk factors for intention, susceptibility, and vaping/smoking. Last, we will explore differential intervention effects and mediators by reporting effect sizes by subgroup.

*Further examination of results.* In additional secondary and sensitivity analyses, we will examine alternative modelling strategies that incorporate class-level effects, the use of alternative indicators or variable codings, and longitudinal models based on all available measurement time points. The quantitative analyses described above will be conducted using RStudio and SPSS. Further details of the statistical analysis plan are available in the pre-registration^37^.

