## Discussion

In this paper, we present a theory- and evidence-based vaping and smoking prevention program resulting from intervention mapping, as well as a protocol for testing its effects in a cluster-randomized controlled trial. Extensive stakeholder engagement enabled the development of a feasible and acceptable intervention that was well received in the feasibility testing. Three interactive workshops taught by graduate students with expertise in medicine and psychology were designed to motivate students to live a vape- and smoke-free life and foster intra- and interpersonal skills necessary to achieve this goal.

The planned cluster-randomized controlled trial is one of the first to evaluate a vaping prevention program using a rigorous research design that reflects the state of the art in behavior change science. Systematically testing mediating mechanisms of change can disseminate future intervention design and enable economic solutions for school-based prevention. However, it must be acknowledged that the present intervention is a complex one, involving multiple BCTs, which limits definitive conclusions about the effect of any single BCT independent of the other techniques used. A viable next step is to complement intervention testing in real-world settings with controlled experiments that allow testing of individual BCTs in isolation^90^.

We will recruit an understudied, diverse sample of students whose high risk of vaping and smoking makes prevention imperative. The baseline survey will collect comprehensive data on the students’ backgrounds, allowing for the examination of differential needs and intervention effects related to students’ SDOH. The study’s findings have the potential to advance precision prevention, thereby leading to improvements in health for all through more personalized intervention approaches. Additionally, the investigation of heterogeneity by SDOH subgroups may offer insights into the underlying structural causes of disparities in vaping and smoking and may inform complementary policy approaches for their reduction. Given the inherent limitations in statistical power when analyzing small subgroups, we consider the planned analyses exploratory in nature; nevertheless, the results have the potential to generate hypotheses on subgroup differences and subsequently facilitate their confirmation in future meta-analyses.

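### Differential programme effects are to be explored only through effect sizes reported per subgroup; the article names no estimate of the difference between subgroups, which is the moderation question it asks

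*Protocol article*

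**What the plan says.** The section on the cluster-randomized trial protocol says the trial will assess "both mediating mechanisms and SDOH as moderators". It lists subgroup factors ("by SDOH subgroups (gender, SES, religion/world view, migration history, spoken language, and health status") for differences in risk factors and outcomes, and continues: "Additionally, we will explore differential intervention effectiveness as well as underlying mechanisms of change by subgroup". The study aims say the results may "provide insights into group-specific needs and inform differentially effective prevention strategies".

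The method is in the Analysis section, under programme evaluation by SDOH: "Last, we will explore differential intervention effects and mediators by reporting effect sizes by subgroup". No treatment-by-subgroup term, contrast or interval for a difference appears anywhere in the article.

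Three further statements bear on how this is read:
- Earlier in the Analysis section, for the regression models in general: "We will investigate intervention effects using the criterion of statistical significance", with p < 0.05 on the treatment coefficient. Secondary and exploratory analyses get no multiplicity adjustment.
- In the closing Discussion: "Given the inherent limitations in statistical power when analyzing small subgroups, we consider the planned analyses exploratory in nature".
- The Analysis section refers further statistical detail to the pre-registration.

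**The concern.** Whether SDOH moderate the effect is a question about a difference between two effects. An effect size in girls and another in boys each describe one group. Neither gives the size of the difference or how precisely it is known. Small subgroups make such estimates scatter, so a table of subgroup effect sizes will often show a pattern when the programme works equally in all groups.

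At stake is the trial's stated use of these results: a precision approach to prevention, and hypotheses about which students need something different. Without the contrast and its interval, a reader cannot tell a chance gap from one worth pursuing. A later meta-analysis of moderation would not receive the within-trial difference and its standard error.

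**Working it through.** **Inputs.** From the section on analytic sample and sample size: d = 0.2, ICC 0.005, 60 students per school, 10 schools per arm (1,200 students), 80% power, alpha 5% (two-sided assumed). Allocation is 1:1 by school. Assumed: subgroup shares, the six listed SDOH factors being the ones used for effect heterogeneity, and their independence. Covariate adjustment is ignored; it would sharpen both approaches.

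**1. The plan's own figure.**
- Individually randomized: 2 × (1.96 + 0.84)² / 0.2², about 393 per arm.
- Design effect: 1 + 59 × 0.005 = 1.295, so 393 × 1.295 = 509 per arm, or 8.48 schools.
- With t quantiles on 2(k − 1) degrees of freedom this becomes 9.53, so 10 schools per arm. Power is 82.1% at 10 and 77.4% at 9.
- 1,200 / 0.80 = 1,500.

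The stated sample size is reproduced. The article gives no corresponding figure for subgroups.

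**2. Gap between two equal subgroups when the true effect is 0.2 in both.** The subgroups share schools, so the school effect cancels in the difference:
- SE = √[0.995 × (4/1,200) × (1/0.5 + 1/0.5)] = √0.01327 = 0.115.
- P(gap ≥ 0.2) = 2Φ(−0.2/0.115) = 0.082 (simulation: 0.084).
- P(gap ≥ 0.1) = 0.39.
- Six independent 50/50 factors: 1 − (1 − 0.082)⁶ = 0.40 for at least one gap of 0.2 or more. Multiplying is reasonable here because the differences on independent balanced factors are nearly uncorrelated.

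With a 70/30 split, the gap reaches 0.2 in 11%. With three equal subgroups the range reaches 0.2 in 33% of trials, and with four in 61%.

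**3. If significance were also read within subgroups.** This is a conditional calculation, because the article does not state such a rule.
- Variance of one half-sample effect: 2 × (0.005 + 0.995/30) / 10 = 0.00763, so SE = 0.087. Power is about 58% in each half.
- Exactly one of two significant: 45% in simulation. If the two results were independent it would be 2 × 0.58 × 0.42 = 49%; shared schools lower it.
- 70/30 split: power 70% and 41%, discordant in 51%.
- Three or four equal subgroups: mixed results in 70% and 78%.
- Six 50/50 factors, all splitting the same students: at least one discordant in about 80%, or about 87% with assumed unequal splits (50, 30, 40, 40, 50 and 20%).

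**4. The interaction contrast.** False-positive rate is about 5% per factor, and about 26% for at least one of six without adjustment. With SE 0.115, the difference detectable at 80% power is 2.80 × 0.115 = 0.32 SD. Power for a true difference of 0.2 is about 41%.

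**5. Sensitivity.** At an assumed ICC of 0.02, discordance falls to 38% (50/50) and 42% (70/30), and gaps of 0.2 stay near 8%. With 13 schools per arm and the same total of students, discordance is 45% and 51%.

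**The case against.** The strongest case against this has four parts.

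- **The sentence plans reporting, not testing.** It sets no p-value and no rule for declaring heterogeneity. This stands. A reader might infer that each subgroup will be tested against no effect and the verdicts compared, but that carries the general p < 0.05 criterion into a paragraph that does not use it. The figures in step 3 apply only under that inference.
- **On the planned metric, one factor rarely misleads badly.** A gap as large as the whole assumed effect arises in 8–9% of trials for one two-level factor. This stands too: apparent heterogeneity is not simply to be expected for a single factor. It becomes common across six factors or with three or more levels. Raising the per-factor discordance to the sixth power, 1 − (1 − 0.45)⁶ = 97%, would be wrong, because all factors split the same students and share one overall estimate. The figure is about 80%.
- **The analyses are declared exploratory and low-powered.** This limits the claims that can follow and so limits the severity. It does not turn two separate estimates into an estimate of their difference. Effect sizes reported regardless of significance can also be pooled later, so harm to meta-analyses should not be overstated.
- **The pre-registration may name an interaction model.** It is not shown, so its silence cannot be asserted. Subgroup effect sizes are compatible with such a model, and with intervals attached they would allow a rough comparison. But the article states its method affirmatively, and that method does not include the contrast.

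**Conclusion.** The point holds as a mismatch between question and stated method. The article asks whether SDOH moderate the effect and fixes an output that does not estimate moderation. With a uniform effect of 0.2 SD, ICC 0.005 and about 1,200 students, a gap of at least 0.2 SD arises by chance in about 8–9% of trials per equal two-level factor, and in about 40% on at least one of six independent 50/50 factors. If significance were also compared within subgroups, discordance would be about 45% per factor and about 80% for at least one of six, against about 5% per factor for an interaction contrast. These sizes rest on the assumed shares, the independence of the factors and unadjusted models.

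The documents do not support saying that the trial will test each subgroup, that it will declare heterogeneity from such tests, or that no interaction is planned anywhere. The primary conclusion is untouched. The change is worth making because the subgroup results have a stated purpose and the repair is small.

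**What to change.** Replace the sentence along these lines: *Differential intervention effects will be explored by adding a treatment-by-SDOH term, one factor at a time, to the mixed model for T4 intention (all students, same covariates, school clustering). The difference in effect between subgroups with its 95% CI is the exploratory result; subgroup effect sizes with 95% CIs are shown as description.* For mediation, contrast the indirect effects between subgroups in the same way, with an interval. If the pre-registration already specifies this, align the article's sentence with it.

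Cost: one sentence and one model term per two-level factor (more for factors with several levels), with no new data. The intervals will be wide: for a 50/50 split only differences near 0.32 SD are detectable with 80% power, so fewer subgroup differences can be claimed. Across six unadjusted factors about one trial in four would still show at least one nominally significant interaction by chance, so the exploratory label should stay.

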### Confidentiality and dissemination

The data protection concept has been developed in accordance with the Berlin Data Protection Act, the German Federal Data Protection Act and the EU General Data Protection Regulation and has been reviewed by the data protection team of the Charité Clinical Trial Office. To link data across surveys, we will only use pseudonyms generated by the participants, and we will not collect any directly identifying information such as names or personal addresses. Pseudonyms will include codes that replace school names. We will store participant data and a list linking school codes to school names separately on password-protected Charité databases accessible only to members of the study team or, in the latter case, to the study coordinators. Paper-based records of participant data, such as questionnaires or informed consent forms for adult participants, will be stored in locked filing cabinets at the study site. Student and parent consent forms, as well as a list of participating students per class, will be kept securely by school personnel and given to the study team for review on site before each assessment. We will ask schools to destroy these documents at the end of the study. We may publish trial results in a variety of forms, including journal articles, academic theses, and conference or media presentations.

## Discussion

In this paper, we present a theory- and evidence-based vaping and smoking prevention program resulting from intervention mapping, as well as a protocol for testing its effects in a cluster-randomized controlled trial. Extensive stakeholder engagement enabled the development of a feasible and acceptable intervention that was well received in the feasibility testing. Three interactive workshops taught by graduate students with expertise in medicine and psychology were designed to motivate students to live a vape- and smoke-free life and foster intra- and interpersonal skills necessary to achieve this goal.

The planned cluster-randomized controlled trial is one of the first to evaluate a vaping prevention program using a rigorous research design that reflects the state of the art in behavior change science. Systematically testing mediating mechanisms of change can disseminate future intervention design and enable economic solutions for school-based prevention. However, it must be acknowledged that the present intervention is a complex one, involving multiple BCTs, which limits definitive conclusions about the effect of any single BCT independent of the other techniques used. A viable next step is to complement intervention testing in real-world settings with controlled experiments that allow testing of individual BCTs in isolation^90^.

We will recruit an understudied, diverse sample of students whose high risk of vaping and smoking makes prevention imperative. The baseline survey will collect comprehensive data on the students’ backgrounds, allowing for the examination of differential needs and intervention effects related to students’ SDOH. The study’s findings have the potential to advance precision prevention, thereby leading to improvements in health for all through more personalized intervention approaches. Additionally, the investigation of heterogeneity by SDOH subgroups may offer insights into the underlying structural causes of disparities in vaping and smoking and may inform complementary policy approaches for their reduction. Given the inherent limitations in statistical power when analyzing small subgroups, we consider the planned analyses exploratory in nature; nevertheless, the results have the potential to generate hypotheses on subgroup differences and subsequently facilitate their confirmation in future meta-analyses.

Randomization at the school level was chosen to reduce the risk of contamination, as all classes within a grade cohort at a school either received the intervention or served as controls. Nevertheless, some residual contamination cannot be excluded, for example via peers, siblings, or social media exposure across schools and grades. In addition, while participating schools were asked not to implement other external vaping/smoking prevention activities during the study period, or to inform the study team if they did so, some influence of additional prevention activities cannot be fully ruled out in a real-world school setting. If such activities are reported, we will describe them transparently and consider their potential impact in sensitivity analyses.

*Further limitations concern sampling and measurement.* In structurally burdened school contexts, parental consent may make study inclusion more difficult and introduce selection bias if students whose parents do not provide consent are systematically underrepresented. This challenge was already identified during the development study and informed efforts to reduce participation barriers, including adapted study information materials, translated video materials, and close collaboration with schools. These efforts will be continued throughout the trial. Finally, relying on self-report measures for all variables is a study limitation due to the potential for bias; however, given the context of burdened schools, we gave priority to feasibility and economy in the study and intervention procedures.

